### Sample Size Calculation for Future Full-Scale RCT

The current sample size is adequate for pilot studies involving group comparisons to assess feasibility and to estimate the variance to determine the sample size for a definitive trial [76].

## Results

This pilot RCT has been funded by the Arthritis Health Professions Association (AHPA). This protocol was approved by the CHEO Research Ethics Board (#17/08X). As of May 11, 2020, recruitment and data collection have not yet started.

## Discussion

### Strengths

This multidisciplinary and multidimensional rehabilitation study is a rigorous, accessible, single-blind, three-arm pilot RCT using the prospective randomized open blinded endpoint design. It involves web-based, innovative, accessible self-management programs for adolescents with JIA similar to those used in previous studies [41,77,78]. The first strength of this study design is that it will include PA activities that are recommended by several rheumatology organizations and may meet adolescent females’ activity preferences. To our knowledge, this is the first study to assess the effectiveness of aerobic dance and yoga on pain management in female adolescents with JIA. It also aims to reduce daily pain intensity and fatigue severity and improve the functional status, self-efficacy, and PA adherence among female adolescents with JIA. The second major strength of this study is that it will use ICTs to deliver these activities and information to youths. The rapid increase in eHealth will appeal to young participants who are already consulting online resources for self-management [79]. This design will be able to overcome time, geographical, and financial constraints. Furthermore, online questionnaires will increase the accessibility and confidentiality of collected outcome measures.

The involvement of a research coordinator, who will be mentored by a team of rehabilitation specialists, is a strength of the study. Rehabilitation specialists play an essential role in supporting community-based self-management programs targeting youths living with chronic conditions, such as JIA [16].

Separate Facebook group pages and individual online consultations using a video-conferencing platform minimized the potential risk of contamination between comparison study groups. Central randomization is ideal for minimizing the potential risk of biases. This proposed pilot RCT is necessary to address the questions of clinical and scientific importance for rehabilitation specialists in improving the health of female adolescents with JIA through the use of PA-based interventions.

### Challenges (or Weaknesses)

The blinding of participants is impossible in this type of study, as is generally the case with physical rehabilitation RCTs [80].

There is an increased risk of Type 1 error, rejecting the null hypothesis when it is actually true, due to the presence of multiple outcomes (ie, multicollinearity). The results of this study will likely only be generalizable to female adolescents (ie*,* those aged 13 to 18 years) with JIA who consult at a pediatric rheumatology clinic in a tertiary care center.

Due to financial limitations, we will use low-cost, accessible ICTs. Although a virtual gym with a live PA instructor would be ideal, participants will have access to recorded sessions led by PA instructors and approved by rehabilitation specialists in rheumatology and will receive support from a research coordinator trained in PA at least once a week.

Hospital-based recruitment may attract more severe cases of JIA. However, central randomization will be implemented as it is ideal to minimize the potential risk of biases.

This study will examine the effectiveness of yoga among female adolescents with JIA, as outcomes will be assessed at 12 weeks.

#### Population

To minimize the potential misclassification bias, rheumatologists involved in this project will ensure that each participant enrolled in this pilot RCT has a diagnosis of JIA, using ILAR criteria [81].

Although participants cannot be blinded to the group assignment given the nature of the intervention, the investigator who will analyze the data will be blinded.

#### Intervention

Aerobic dance [30] and yoga exercise programs [26-28,58] are promising for managing JIA pain in young women because they are popular among female adolescents [23-25,30]. These programs will be accessible and inexpensive through Facebook and YouTube [51,79,82].

#### Comparator

The use of an electronic pamphlet control group is acceptable as they will have access to Facebook and will have online consultations on PA. Furthermore, participants will receive the same yoga or aerobic dance exercise videos that were offered to the intervention groups after study completion.

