**Methods:**

A three-arm prospective randomized open-label study with a parallel group design will be used. A total of 25 female adolescents with JIA who have pain will be randomized in a ratio of 2:2:1 to one of the 3 groups: (1) online yoga training program (group A: n=10); (2) online aerobic dance training program (group B: n=10); and (3) electronic pamphlet control group (group C: n=5). Participants in groups A and B will complete 3 individual 1-hour sessions per week using online exercise videos, as well as a 1-hour virtual group session per week using a videoconferencing platform for 12 weeks. Participants from all groups will have access to an electronic educational pamphlet on PA for arthritis developed by the Arthritis Society. All participants will also take part in weekly online consultations with a research coordinator and discussions on Facebook with participants from their own group. Feasibility (ie, recruitment rate, self-reported adherence to the interventions, dropout rates, and percentage of missing data), acceptability, and usability of Facebook and the videoconferencing platform will be assessed at the end of the program. Pain intensity, participation in general PA, morning stiffness, functional status, fatigue, self-efficacy, patient global assessment, disease activity, and adverse events will be assessed using self-administered electronic surveys at baseline and then weekly until the end of the 12-week program.

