### Study Design

This study will use a three-arm prospective randomized open-label study. Participants will be randomized to one of the 3 following groups in a ratio of 2:2:1: group A: an online yoga training program (and a PA electronic educational pamphlet; n=10); group B: an online aerobic dance training program (and a PA electronic educational pamphlet; n=10); and group C: an electronic pamphlet control group (PA electronic educational pamphlet; n=5). The total intervention period will be of 12 consecutive weeks. The frequency and duration of the interventions are based on other trials of yoga and PA interventions in pediatric and adult rheumatology [18,20,22,26,58]. As this pilot RCT involves physical interventions (ie*,* yoga and aerobic dance training programs), the participants and the research coordinator administering the program will not be blinded. However, the use of anonymous online self-reported questionnaires administered at baseline and postintervention will reduce potential detection bias. With training and standard operating procedures in place, it is anticipated that any performance bias due to not blinding will be minimized.

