### Interventions

#### Group A

Participants assigned to this group will be invited to complete a yoga training program. The yoga training program, an evidence-based educational program, is a structured low-intensity Vishwas Raj [26]. This yoga program consists of stretching, strengthening, meditation, and deep breathing and has been shown to be acceptable and effective among adults with RA. Participants will be asked to complete 3 individual 1-hour sessions per week for 12 consecutive weeks by watching a previously filmed session led by a qualified yoga instructor and posted on Facebook. They will also take part in a 1-hour virtual group session per week using a video-conferencing platform. Participants will also participate in weekly online consultations with a research coordinator and discussions on Facebook with other participants in group A. Finally, participants will receive an electronic pamphlet on physical exercise developed by the Arthritis Society. The electronic pamphlet, which groups B and C will also receive, explains how PA can help manage arthritis. It includes valuable tips and a detailed list of the various types of PA and exercises.

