#### Group B

Participants assigned to this group will receive the electronic pamphlet on physical exercise and will be invited to complete an aerobic dance program. The aerobic dance program is a low-to-moderate intensity–level program and will also use a video. The video, adapted for youths with JIA, was developed with feedback from a JIA patient with experience in aerobic dance and a physiotherapist with experience in pediatric rheumatology. The aerobic dance program will have the same characteristics in terms of frequency, total number of sessions, and total duration as the yoga program (ie*,* three 1-hour individual sessions and one 1-hour virtual group session per week for 12 weeks). Participants will also participate in weekly online consultations with a research coordinator and discussions on Facebook with other participants in group B.

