Participants will be invited via Facebook and email to attend an individual online consultation with the research coordinator using a videoconferencing platform. During this consultation, participants can ask questions related to their group assignment, voice their concerns, and establish a plan of action. For the remainder of the study duration, participants will be encouraged to attend, when possible, individual 10-minute online consultations weekly. During these consultations, participants can provide their feedback and discuss their use of the PA program as well as facilitators and barriers to participating. Private meetings are less difficult to schedule than group meetings and provide greater privacy. They may also be more motivating and less intimidating for participants who may feel their voice really matters and has an impact.For the study duration, participants will be asked to complete 3 individual exercise sessions as well as 1 virtual group session each week. The links to the videos will be posted on Facebook and sent by email for participants to use for their individual exercise sessions. For group sessions, the videoconferencing platform link will be posted on Facebook and sent to participants via email. Virtual group sessions will help ensure that they perform the exercises that they observe in the video safely and that they do not hurt themselves. They will also be able to see other participants and be seen if they wish, which will be a motivating factor to perform the PA. A schedule of virtual group sessions offered in the morning or afternoon will be posted on the Facebook group page or sent by email.Participants will be asked to record their PA using a validated exercise log [61] as well as their pain intensity and fatigue by completing a brief online questionnaire that regroups valid instruments on a weekly basis. They will be reminded to do so via Facebook, email, and during their online consultations.

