### Conclusions

This pilot RCT has substantial potential to enhance our understanding of the potential effectiveness of popular PA interventions disseminated to patients with JIA using ICTs, making it a novel study. This will help understand which PA intervention has the most potential for improved outcomes. It will also help determine whether these PAs and ICTs are acceptable to youths with JIA and whether a larger trial would be feasible. The proposed pilot RCT will contribute to the knowledge of the effect of a specific functional activity on self-reported pain relief, functional status, and self-efficacy as well as PA adherence, daily pain, and fatigue intensity.

This study could also set the standard for community-based care for female adolescents with JIA. Moreover, other rehabilitation or functional interventions could be examined for youths with other chronic diseases**.**

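### Weekly-form reminders are stated for the exercise arms only, and the comparison with control estimates the delivered package, not the activity itself

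*Protocol article*

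**What the plan says.** **Reminders.** All three groups are asked to fill in a brief weekly questionnaire covering the exercise log, pain intensity and fatigue (Participant Allocation). For groups A and B the text adds: "They will be reminded to do so via Facebook, email, and during their online consultations". The group C paragraph makes the same request and stops there. Outcome Measures then covers everyone: updates and reminders about questionnaire deadlines go on the Facebook wall or the hospital webpage, and all three groups are emailed the same questionnaire link.

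**Contact.** For group A: "They will also take part in a 1-hour virtual group session per week using a video-conferencing platform". Group B has the same pattern: "three 1-hour individual sessions and one 1-hour virtual group session per week for 12 weeks". All groups are also encouraged to attend a weekly 10-minute individual consultation where possible. Group C has the consultation, the pamphlet and its own Facebook page, but no group session.

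**Interpretation.** The Comparator section defends the control: "The use of an electronic pamphlet control group is acceptable as they will have access to Facebook and will have online consultations on PA". The secondary objective concerns the initial effectiveness of each training program against the pamphlet group. The Conclusions go further and say that the trial will "contribute to the knowledge of the effect of a specific functional activity on self-reported pain relief".

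**The concern.** Two separate matters arise.

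First, the percentage of missing data in the questionnaires is one of the primary feasibility measures. If two arms are prompted by three routes and the third only by a wall or webpage posting, part of any difference in form completion would come from trial procedure. Planning for the full-scale trial would then rest on a figure that mixes willingness to respond with intensity of prompting. The activity log is collected through the same weekly form and is exposed in the same way.

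Second, the defence of the comparator lists only elements that all arms share. It leaves out the group session, which the protocol itself describes as motivating (Participant Allocation) and as a possible aid to adherence (Time). Participants are unblinded, and pain, fatigue and self-efficacy are self-reported. A difference from control could therefore reflect the exercise, the live group contact, or both, and the Conclusions credit it to the activity.

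**Working it through.** **1. Reminders, side by side.**

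| Channel for the weekly form | Groups A and B | Group C |
|---|---|---|
| Facebook wall or hospital webpage | stated | stated (Outcome Measures, all groups) |
| Email | reminder stated | questionnaire link stated, reminder not stated |
| During the weekly consultation | stated | not stated |

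The clearest difference is the reminder given in the consultation. The email difference is weaker, because group C does receive an email with the link.

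**2. What the difference can reach.**
- Data Analysis compares the groups at 0, 6 and 12 weeks. The week 6 and 12 questionnaires on pain, functional status, fatigue, self-efficacy and well-being go to all participants, under the common reminders. They are largely outside the disputed sentence.
- The exercise log is completed weekly and supplies activity duration and intensity, so it is exposed.
- The missing-data measure is monitored continuously for up to 12 weeks, so it is exposed.
- For protocol deviations and dropouts, Outcome Measures says that the group will be recorded. For missing data it lists time and reasons, but not group.

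**3. How missingness behaves at these arm sizes.** The 2:2:1 allocation of 25 gives 10, 10 and 5. With one form per week for 12 weeks:
- A: 10 × 12 = 120 forms. B: 120. C: 5 × 12 = 60. Total 300.
- One participant who never responds is 12/60 = 20% of the forms in C, but 12/120 = 10% in A or B.
- C supplies 60/300 = 20% of all forms, so each extra 10 percentage points of missingness in C raises the pooled figure by only 2 points. A pooled percentage would hide a difference between arms.

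The documents give no completion rate by arm or by reminder, so the size of any effect of prompting cannot be calculated.

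**4. Scheduled live contact.** Inputs: 12 weeks (Study Design), a 60-minute group session in A and B, and a 10-minute consultation in all arms.
- A or B: 12 × (60 + 10) = 840 min = 14 h, in 24 contacts.
- C: 12 × 10 = 120 min = 2 h, in 12 contacts.
- Ratio in minutes 840/120 = 7.0; ratio in contacts 24/12 = 2.0; excess 720 min = 12 h per participant.

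The protocol states no contact ratio of its own to reproduce. Seven is the scheduled maximum, and two unstated quantities change it:
- Length f of the first consultation (assumed): (f + 110 + 720)/(f + 110) gives 6.5, 6.1 and 5.2 for f = 20, 30 and 60 min.
- Group-session attendance a (assumed, with full consultation attendance): (720a + 120)/120 gives 5.5, 4.0 and 2.5 for a = 75%, 50% and 25%.

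The imbalance remains in every case. A and B have the same schedule, so the comparison between them is matched on contact.

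**The case against.** The strongest reply on contact is that the group hour is treatment. It is one of four prescribed weekly sessions, participants exercise during it, and being seen by others is optional. Counting it as a confounder would treat dose as bias. Group C also has peer contact through its own Facebook page, and a pamphlet control is a legitimate choice. All of this stands. A reader might infer from the sevenfold figure that the comparison with control is invalid. The documents do not support that, because the Objectives already frame it as training program versus pamphlet, and the contrast estimates exactly that. What survives is narrower: the Comparator section does not mention the unmatched session, and the Conclusions name the activity instead of the program.

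On reminders, the reply is that silence in one paragraph of a condensed article does not show that group C goes without. Outcome Measures promises reminders to all, emails the link to all, and group C has the same weekly consultation in which a reminder could be given. This also largely stands. A reader might infer that missing data will differ by arm and bias the clinical results. The text establishes neither: nothing says that group C receives no email or spoken reminder, and the main clinical measurements at weeks 6 and 12 fall under the common arrangements. What remains is that two paragraphs written in parallel differ on a procedure that feeds a primary feasibility measure.

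Finally, this is a pilot whose primary aims are feasibility and acceptability. That limits the weight of the contact point, which touches the secondary objective. It does not limit the reminder point, which touches a primary one.

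**Conclusion.** The point holds in limited form.

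Read literally, the protocol prompts A and B for the weekly form through routes that it does not state for C. This could distort the percentage of missing data and the weekly activity log. It is a possibility created by the text, its size is unknown, and it largely spares the analysis at weeks 0, 6 and 12.

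On contact, A and B are scheduled for up to 840 live minutes against 120 in C. The figure assumes full attendance and a first consultation of 10 minutes; under the other assumptions tried, the ratio runs from 2.5 to 6.5. The A versus C and B versus C contrasts are valid for the delivered package but cannot isolate yoga or dance from the group contact that comes with it. A versus B is unaffected, and the Objectives need no change.

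**What to change.** 1. **Participant Allocation and Outcome Measures:** reconcile the reminder text so that all three arms receive the same reminders for the weekly form, through the same channels (Facebook or webpage, email, consultation) and on the same schedule.
2. **Outcome Measures:** add group to what is recorded for missing data, as is already done for deviations and dropouts, and report missingness by arm with counts, given five participants in C.
3. **Comparator:** state that the control does not match the weekly group contact of A and B.
4. **Conclusions:** replace the reference to the effect of a specific activity with the effect of each program as delivered, compared with the pamphlet and consultations.

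The reminders use channels that the trial already runs, so the cost is close to nil. The wording changes narrow the stated conclusion to what the design can show. No arm, session or sample size changes. The Results section says that recruitment had not begun as of May 11, 2020; on that status, all four changes can be made before any data are collected.

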#### Outcomes

Assessments will include a range of clinical outcome measures validated in JIA. Although pain and other outcomes are self-reported, they represent important unwanted symptoms that have functional consequences that affect the activities of daily living of youths with JIA. Furthermore, objective measures of these symptoms are difficult to obtain. However, it is important to be mindful that self-reported measures may lead to reporting bias.

There is also the potential to include further measurements such as PA level (using a questionnaire or an accelerometer) and aerobic exercise testing (ie*,* assessment of submaximal oxygen consumption: PWC_170_, physical working capacity at a heart rate of 170 beats per min) to determine potential differences between treatment arms in the full-scale RCT.

#### Time

The study duration will be 12 consecutive weeks. The frequency and duration of the intervention is based on other trials of yoga and PA interventions in pediatric and adult rheumatology. This length is sufficient to see improvements among adolescents.

Providing participants with weekly online consultations with the research coordinator and providing them with 1 virtual group session each week will help ensure that the participants perform the exercises properly and may also potentially facilitate adherence.

If the proposed PA interventions are effective, we will produce videos to enrich the People Getting a Grip program, an online educational program comprising informational videos and practical videos that provide information on various PA programs for arthritis. These videos will also be freely available on the Arthritis Society webpage and could eventually be used for the full-scale RCT.

### Conclusions

This pilot RCT has substantial potential to enhance our understanding of the potential effectiveness of popular PA interventions disseminated to patients with JIA using ICTs, making it a novel study. This will help understand which PA intervention has the most potential for improved outcomes. It will also help determine whether these PAs and ICTs are acceptable to youths with JIA and whether a larger trial would be feasible. The proposed pilot RCT will contribute to the knowledge of the effect of a specific functional activity on self-reported pain relief, functional status, and self-efficacy as well as PA adherence, daily pain, and fatigue intensity.

This study could also set the standard for community-based care for female adolescents with JIA. Moreover, other rehabilitation or functional interventions could be examined for youths with other chronic diseases**.**

